##### Dual-task walking

The modified SST and VFT are performed during preferred walking speed using the Optogait system. During dual-task walking, participants are instructed to keep walking even if they cannot solve the cognitive task. The selection of the dual-task conditions is based on current research [19, 53].

#### Balance tests

To measure balance tasks, we implement a self-built, customized balance setup test (Fig. 2). The balance setup is made up of a force-platform (IMM Holding GmbH, Germany; 1 kHz), which is installed directly on top of the bottom-platform of a Posturomed device (Haider Bioswing GmbH, Germany). The force-platform is also equipped with heating elements to keep the surface temperature at 25 °C. The bottom-platform of the Posturomed is mobile in the horizontal direction and suspended vertically. To perform quasi-static tests, the bottom-platform is locked in place, so as to prevent movements. To enable unexpected perturbations (dynamic balance tasks), the Posturomed is equipped with an electro-magnet, which holds the bottom-platform in place after shifting it 20 mm out of its neutral position, according to Germano et al. [33]. Unexpected perturbations are induced by manually triggering the electro-magnet, causing the bottom platform to be released and to swing until it again reaches the neutral position. Moreover, the setup also includes a single axis accelerometer ADXL78 (Analog Devices Inc., USA), which is used to detect the reversal points of the oscillating bottom-platform. Participants are secured with a safety belt during all balance tests, which is a built-in safety feature included to prevent falls or other injuries. The balance setup exhibits a good inter- and intra-day reliability [78].

**Fig. 2 Fig2:**
[figure not shown]
Balance set-up with Posturomed, force-platform, and safety belt

##### Quasi-static balance tests

Participants perform two different balance tasks to measure quasi-static abilities. The first balance task tests participants’ quasi-static balance ability during three conditions: double leg stance (eyes opened and eyes closed) and single leg stance (eyes open). For the double leg stance tests, trials of 25 s are performed and participants are instructed to keep their knees straightened but not locked, and to keep their arms hanging down. They are also asked to evenly distribute their body weight on both feet, keeping them hip width apart. For single leg stance tests, trials of 12 s are collected and participants are asked to stand on their dominant leg while flexing their contra-lateral lower limb backwards and keeping their upper limbs hanging down. To become accustomed to the apparatus, participants perform one practice trial per condition. Then, three trials per condition are collected for data analysis in randomized order.

The second quasi-static balance task is the so-called Limits-of-Stability-Test [79]. Participants are asked to stand as still as possible in their normal posture, with their arms by their sides and eyes opened. After an acoustic signal from the experimenter, they lean forward as far as possible and stay inclined for 10 s. Inclinations are accomplished without lifting toes or heels, and with minimal bending at the hip or knees. Furthermore, the trunk is kept almost straight. One practice trial is performed and another three valid trials are included for data analysis.

##### Dynamic balance tests

The dynamic balance tests investigate the ability to withstand unexpected perturbations in the medio-lateral and anterior-posterior directions [33, 78]. Participants are instructed to look straight ahead while keeping their knees straightened but not locked, and to keep their upper limbs hanging down at both sides, eyes opened. Feet are positioned hip-width apart at the center of the plate. After the experimenter presses a manual trigger, the bottom platform is released, initiating the unexpected perturbation. Subsequently, the bottom platform swings horizontally until it again reaches the neutral position. Participants are asked to maintain or regain their balance while the platform is in motion. The dominant foot is positioned towards the electro-magnet during the tests in the medio-lateral direction. For the anterior-posterior direction, participants stand on the plate with their heels pointing toward the electro-magnet. To become accustomed to the apparatus, each participant performs six trials (three in each direction) before data collection begins. Collecting in a randomized order, the three following valid trials per condition are included in the data analysis.

#### Fine motor tasks

Participants carry out three fine motor tasks: (1) force modulation of a precision grip with thumb and index finger (similar to the set-up of Voelcker-Rehage and Alberts [80]), (2) tapping with the index finger of the dominant hand (based on Rabinowitz and Lavner [38]), and (3) connecting dots on a touchscreen with a touch pen / tracing (as studied by Yan [81]).

To collect data for the fine motor task (1), two compression load cells with a diameter of 29.5 mm, a depth of 8 mm, and a measurement range of 0–22.5 kg (Manufacturer: Measurement Specialties Inc., Hampton, VA, USA; Model: FX-1901-0001-50 L) are used (cf. [82] for comparable unimanual setup). Signals are pre-amplified (using a customized voltage amplifier), digitally converted, and sampled at a frequency of 120 Hz, using a NI-DAQ USB-6002 (National Instruments, Austin, TA, USA). For programming the experimental procedures, i.e., data acquisition and real time visual feedback, a customized LabView 2015 (National Instruments, Austin, TA, USA) script is used. Force transducers are placed on a table in front of the participants, which are seated at a distance of 60 cm in front of a 23.8 in. monitor (hardware resolution 1920 × 1080 pixels). This monitor produces real-time feedback about actual force levels of the participants and target forces that need to be met (see Fig. 3). Feedback about the magnitude of the applied force to both sensors is indicated by two small dots that move up when more force is applied and down when less force is applied. Squares (width and height: 12.5 mm) are displayed on the screen to indicate reference values (see Fig. 3). The scale of the display is adjusted with respect to individual force ranges and the size of the target box corresponds to 0.6% of maximum voluntary contraction (MVC). The aim of the force modulation of a precision grip task is to assimilate the force to a sine wave (ranging from 5 to 12% of MVC of the dominant hand). In our task, the target sine wave is visualized on the screen by the squares which, depending on the condition, are either moving up and down (frequency 0.2 Hz) or are held constant. Participants have to modulate their force to try and keep the dot in the box. This task is performed bimanually and unimanually. The bimanual condition consists of 34 trials (20 s each) overall and includes five conditions: (1) inphase – the target sine waves move simultaneously; (2) antiphase – the target sine waves move inversely, when the right sine wave is on the maximum, the left sine wave is on the minimum; (3) constant – a constant symmetric force with both hands at 12% of MVC (boxes do not move), (4) left hand applies a constant force at 12% of MVC and the right hand follows an alternating sine-wave force pattern between 5 and 12% of MVC, and (5) right hand applies a constant force at 12% of MVC while the left hand follows an alternating sine-wave force pattern between 5 and 12% of MVC.

**Fig. 3 Fig3:**
[figure not shown]
Set-up for fine motor task “force modulation”

For the fine motor task (2) “finger tapping”, one of the two force transducers from the previous task is used. The force transducer is fixed in a self-built wooden board which is placed on the table in front of the participants to prevent any movement of the transducer during the task (see Fig. 4). Experimental procedures, i.e., data acquisition, were programmed using a customized LabView 2015 (National Instruments, Austin, TA, USA) script. The task is to tap with the dominant index finger on the force transducer, which participants carry out in two different conditions: as consistently as possible at a self-selected pace, and tapping as fast as possible with disregard to consistency. Each trial lasts 15 s, with three trials in the first condition and two trials in the second condition. There is no visual feedback for the participants.

**Fig. 4 Fig4:**
[figure not shown]
Set-up for fine motor task “finger tapping”

For the fine motor task (3) “connecting dots / tracing”, a touch monitor (Manufacturer: Hannstar Display Corp., 23.0 in., hardware resolution 1920 × 1080 pixels, Taipei City, Taiwan; Modell: HSG 1353) and a touch pen (WACOM Bamboo-Stylus Alpha CS-180, length 130 mm, diameter 9 mm, weight 12 g) are used. The monitor is placed horizontally on a table in front of the participants. The pen is held in the dominant hand (see Fig. 5). Experimental procedures, i.e., data acquisition and real time visual feedback, were programmed using a customized LabView 2015 (National Instruments, Austin, TA, USA) script. Participants have to connect dots on the touchscreen (black desktop background) via the touch pen by drawing a white line. There are two tasks: tracing a straight line and tracing a curved line. Two green dots (diameter 15 mm) are shown in the straight line setting, which are marked with 'Start' and 'Target', one above the other (see Fig. 5). Furthermore, there are two different distances (50 mm and 200 mm) between the start and target dots. In addition, a third white in-between-dot (diameter 12.5 mm) is presented half way between the start and target dots in each condition (horizontal distance 25% of that distance (12.5 mm or 50 mm) to the right) in the curved line setting, which the participants have to draw through (see Fig. 5). Overall, four conditions (straight line short, straight line long, curved line short, and curved line long) with seven trials are completed in randomized order.

**Fig. 5 Fig5:**
[figure not shown]
Set-up for fine motor task “connecting dots / tracing”

#### Foot-eye coordination tests (pedal)

Foot-eye coordination (foot proprioception) is investigated using self-constructed pedals for the right and left feet (Fig. 6). The pedals are equipped with a gas spring (Febrotec, Nitrider® 0GS-N06AAA0050, Halver, Germany) and a linear potentiometer (Vishay Electronic GmbH, 249FGJS0XB25, 1kohm, Landshut, Germany). With a starting position of 45° dorsiflexion with respect to the horizontal floor, the pedals can be freely rotated within a range of ±20°. The analog data of the potentiometer is converted to digital signals using an AD card (Measurement Computing, USB-231, Bietigheim-Bissingen, Germany). A flat computer screen (24 in., 16:9) is positioned approximately 100 cm in front of the participant. The foot-eye coordination task is an accuracy task, in which participants are requested to reproduce given curves using their foot (right and left, separately). Visual feedback is provided on the screen using a routine in LabView 2015 (National Instruments Corp., Texas, USA). During plantar or dorsal flexion, the rotation of the pedals (pressing or depressing the pedal) generates live control of the line on the screen. Participants are instructed to reproduce the displayed curve as precisely as possible. The visual feedback begins as soon as the pedals are pressed.

**Fig. 6 Fig6:**
[figure not shown]
Set-up for foot-eye coordination

For the foot-eye coordination tests, participants are instructed to sit comfortably, keeping their knees and hips at 90°, placing their feet on the pedals, and adjusting the distance between the chair and the pedals. Participants are instructed to reproduce given curves using their foot (right and left, separately) to operate the pedals. For each trial, ten sinusoidal curves at two different frequencies are displayed as a continuous graph. One test-trial per foot is performed. After the test-trial, three trials per foot are collected in a randomized sequence. Foot temperatures at the first metatarsal head (Met1) are measured before and after testing. Note that the three trials did not seem to be sufficient to promote long-lasting and relevant practice effects. Even with training sessions, a study of Teasdale et al. [83] exhibited no long-term retention in learning processes for MCI.

#### Functional status and physical performance

Functional status and physical performance is assessed using the Short Physical Performance Battery (SPPB), a standardized instrument which includes tests for (1) balance (legs closed / feet together, semi-tandem stand, tandem stand), (2) comfortable gait speed over four meters, and (3) chair raising test (five times sit-to-stand transfer) [84]. Each test is scored between 0 and 4, the total score ranges from 0 (low mobility/functionality) to 12 (full mobility / functionality).

Additionally, cardiovascular fitness is measured using the 2-min step test [85]. Therefore, the OA step in place as often as possible in 2 min. All steps with the right leg are scored.

Hand Grip Strength is assessed using the digital grip dynamometer (Grip D®, Takei scientific instruments, Niigata City, Japan). Three assessments are executed with the right and the left hand with a straightened elbow [86].

We also collect data for height, weight, and body fat using a stadiometer (seca213, seca Deutschland, Hamburg, Germany) and a bioimpedance scale (Tanita InnerScanV, Model BC-545 N, TANITA Corporation, Tokyo, Japan).

### Sensory measures

#### Visual acuity

The Freiburg Visual Acuity Test [87] with Landolt C is used to measure visual acuity. The participants are placed exactly 3 m from the screen and complete 18 trials. The measurement is carried out with vision aid to measure corrected vision.

#### Hearing

To measure corrected hearing ability, four lists of the Freiburg monosyllabic test (part of the Freiburg speech test [88]) are presented without background noise via headphones. Four different sound levels (35 dB, 47 dB, 24 dB, 53 dB) are used in the same order for all participants.

#### Vibration perception thresholds

To assess skin sensitivity, vibration perception thresholds (VPTs) are measured using a Tira Vib vibration exciter (model TV51075, Schalkau, Germany) (Fig. 7), which presents good reliability [89]. Vibration from the exciter is applied to the foot location by a metal probe (rounded, 7.8 mm diameter) protruding through a hole (2 mm above surrounding surface level), according to [32, 90]. The surface of the vibration exciter is an aluminum platform equipped with heating elements to maintain the surface at a constant temperature (in this case 25 °C), to avoid skin temperature fluctuations. Vibration amplitude (in μm) is detected using an accelerometer (MMA2241KEG, NXP Semiconductors). The frequency of the vibrating contactor is set at 30 Hz and 200 Hz, which are known to be the optimal stimuli to elicit Meissner corpuscles and Vater–Pacini corpuscles, respectively [91]. The vertical force applied from the participants’ feet toward the probe is monitored via a force transducer and kept within a range of ± 0.5 N. Acoustic noise cancelling headphones (Bose® QuietComfort 25) are used to ensure that there is no distraction during the measurements.

**Fig. 7 Fig7:**
[figure not shown]
Left: Vibration perception threshold set-up for measuring hand and foot sensitivity. Right: Platform with tip of vibrating probe (black squares)

##### Vibration perception threshold tests

First, sensitivity tests at the fingertip are performed. Participants are instructed to sit in a standardized manner but also comfortably, to be able to concentrate on detecting the vibration stimuli. The fingertips rest on top of the metal probe, without exerting additional pressure. Furthermore, participants wear acoustic noise cancelling headphones. Before starting the tests, test-trials are performed to define the value of the starting amplitude for the consecutive trials. The protocol for measuring VPTs is similar to a method of limits approach introduced by Mildren et al. [92].

In short, vibrations are introduced above the threshold, so that they can be clearly perceived by the participants (start amplitude defined according to test-trials). For each trial, a sequence of vibrations with different amplitudes (with randomized pauses in between) is applied and participants are asked to push a hand-held button as soon as they perceive each vibration stimulus. After pressing the button, the intensity of the previous, perceivable vibration stimulus is halved. When a vibration stimulus is not perceived, the next stimulus is delivered at half the intensity of the unperceived and the previously perceived stimuli. Then, four more stimuli are delivered to determine the final VPT. In total, three VPT-trials are collected at the fingertip of the index finger (at 30 Hz). Skin temperatures at the fingertip are measured before and after the three trials. After the hand sensitivity tests, the same protocol is performed to test foot sensitivity at the first Metatarsal head (at 30 Hz and 200 Hz).

### Questionnaire battery

Participants need to complete a questionnaire battery, which includes the following secondary outcome parameters: frailty, physical activity, social support, social activities, depression, comorbidities, health behavior, quality of life, and handedness. The self-administered questionnaire contains validated instruments and self-generated items which are shown in Table 4. Sociodemographic information includes age, sex, education, and employment.

**Table 4 Tab4:** Outcome measures in the self-administered questionnaire

Outcome measure	Instrument/scale
**Physical activity**	
Physical activity	Modified Baecke Inventory (similar to [93]) PRISCUS-Physical Activity Questionnaire [94] Nürnberger-Alters-Inventar (NAI) [95]
**Social support, social activities**	
Social support	Social Support Questionnaire - short form [96]
Social activities	Florida Cognitive Activities Scale (modified [97])
**Health behavior**	
Objective health	List with diseases and use of medication (modified [98])
Comorbidities	Charlson Comorbidity Index [99]
Chronic medication	Individual medication regimen (name, dosage and frequency of intake for all prescribed medication)
Frailty	Frail Scale [100, 101] Tilburg Frailty Indicator [102, 103]
History of falls	Elderly Fall Screening Test (modified [104])
Falls efficacy	Fall Efficacy Scale [105]
Smoking behavior	Smoking Behavior Questionnaire [106]
**Quality of life and well-being**	
Quality of life	Satisfaction with Life Scale [107]
Depression	Geriatric Depression Scale [108]
Personality	Big Five Inventory [109, 110]
**Handedness**	
Handedness	Edinburgh Handedness Inventory [111]
Manual activities	Manual Activities Questionnaire [112]

### Data collection and management

Participant information will be recorded by a coded ID number. Hard copy forms will be stored in locked cabinets accessible only by project staffs. Electronic data will be stored on a secured computer that is password-protected. The databases will not contain subject identifiers and the data linking subject identifiers and the subject ID code will be stored separately.

Data quality will be promoted by double data entry and range checks for data values.

Only project staffs will have access to the final trial dataset.

### Data monitoring

A data monitoring committee, responsible for data monitoring, interim analyses, and auditing, will not be established, because no adverse events are to be expected. However, study participants will be under the surveillance of trained project staff who will intervene if a negative reaction is observed during the measurements.

### Sample size

The sample size calculation was based on the outcome cognitive decline. Based on literature [47, 51] small to moderate effect sizes are expected. Statistical power analysis using G*Power (Version 3.1.9.4, Franz Faul, University of Kiel, Germany) showed that 200 participants are required for analysis with α = .05 and power = .80. Expecting a 20% dropout rate during the study period, 240 participants will be included.

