## Methods

### Study aims

The following main research question investigated in this study is:

Which cognitive, sensory, motor, and neurophysiological variables are predictors of the transition from subjective cognitive impairment or MCI to dementia in comparison to age-matched healthy OA?

The objective of the SENDA study is to develop a multi-dimensional sensor-based instrument based on the stated variables or their combination to detect cognitive decline or dementia in OA.

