#### Cognitive status

All prior introduced neuropsychological assessments are used to establish the cognitive status of each participant at baseline and each follow-up. All criteria including cut-offs can be found in Table 3. Cognitive decline is defined as a change from CHI to SCI, pMCI, or MCI, as well as a change from SCI to pMCI or MCI or from pMCI and MCI to dementia. Individuals are categorized as having dementia when they receive a clinical dementia diagnosis outside of the study at any follow-up. Furthermore, participants are categorized as having dementia if they score less than 19 points in the MoCA [62] and perform worse than 1.5 SD below the norm in multiple cognitive domains of the CERAD-Plus. If so participants are advised to visit their general practitioner for further evaluation regarding dementia and to give a feedback to the study coordinator of SENDA as soon as possible. Additionally, functional limitations in ADL and the presence of depression will also be taken into account (see section ‘Questionnaire battery’).

**Table 3 Tab3:** Criteria for cognitive status of the participants

Group	Cognitive Status	Measures		
		MoCA	CERAD-Plus	Flei
Group 1	CHI	30–26	All tests within normal range (≤ 1.5 SD)	≤ 30
Group 2	SCI	30–26	All tests within normal range (≤ 1.5 SD)	> 30
Group 3	pMCI	30–26	1 or more tests below normal range (≥ 1.5 SD)	not considered
		< 26	All tests within normal range (≤ 1.5 SD)	not considered
	MCI	< 26	1 or more tests below normal range (≥ 1.5 SD)	not considered

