### Statistical analyses

A multiple regression model (with e. g. ordinary least squares technique) is used to detect several predictors or mediators of cognitive decline. To identify the most parsimonious model, and with it the final predictors, we analyze the corresponding coefficients of determination and consider the multiple comparisons problem providing a proper method to counteract it. Additionally, we propose an alternative classification taking hand of the k-nearest neighbors algorithm. Furthermore, we analyze changes in motor, sensory, electroencephalogical, and cognitive parameters over time in all three groups using mixed-effects models to explain the correlations in repeated measures in the same subject. Hazard ratios of progressing to dementia for participants with cognitive, motor, sensory, and neurophysiological decline are obtained in the classical way using the Cox semi-parametric proportional hazard model. Several variables are included as potential confounders, such as sex, age, education, comorbidities, psychological status, and social support. The most appropriate procedure for handling missing data will be selected after inspecting the amount and pattern of missing data.

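### The stated 80% power is for cognitive decline, not for the main research question of transition to dementia, and the definition of decline omits SCI to dementia and CHI to dementia

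*Protocol article*

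**What the plan says.** Under Study aims, the main research question concerns "predictors of the transition from subjective cognitive impairment or MCI to dementia", in comparison with age-matched healthy older adults. The next sentence gives a wider objective, an instrument "based on the stated variables or their combination to detect cognitive decline or dementia in OA".

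Under Sample size there is one calculation. It opens with "The sample size calculation was based on the outcome cognitive decline", says that "small to moderate effect sizes are expected", and arrives at 200 participants for analysis (α = .05, power .80) and 240 enrolled.

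Under Cognitive status, decline is any of several worsenings of category. "Cognitive decline is defined as a change from CHI to SCI, pMCI, or MCI" is the first part; the rest is "a change from SCI to pMCI or MCI or from pMCI and MCI to dementia".

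Under Statistical analyses, a multiple regression addresses cognitive decline. "Hazard ratios of progressing to dementia" come from a separate Cox model. The article gives no dementia rate, event count or hazard ratio.

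**The concern.** The question called main and the outcome that was powered are not the same. Decline as defined can be reached without any approach to dementia. By Table 3, a move from CHI to SCI needs only a FLei score that rises above 30 while MoCA and CERAD-Plus stay normal. Dementia is one component of decline and presumably a less frequent one. The power of a Cox model depends on the number of dementia events, which the sample size section does not consider.

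With few events, a null result for a marker would say little, and a marker that stands out could do so by chance. The study is meant to lead to a screening instrument, so it matters how firmly a dementia result can be read.

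The definition of decline adds a second problem. The main question includes SCI to dementia, yet the list of changes that count as decline does not.

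**Working it through.** **1. The plan's own figure.** N = 200 cannot be reproduced uniquely, because the test, the number of predictors and the numeric effect size are not given. It is plausible for effects described as small to moderate. At 80% power and α = .05, 200 participants correspond to f² of about 0.040 for one coefficient, or 0.066 for a joint test of 5 predictors. Nearby cases are r = 0.20 (N = 194) and a three-group ANOVA with f = 0.22 (N = 203). None of these is a time-to-dementia calculation.

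**2. Follow-up that the design allows.** Table 2 gives Cohorts 1 to 4 four, three, two and one visits, at intervals of 8 months:
- Cohort 1: 3 × 8 = 24 months
- Cohort 2: 2 × 8 = 16 months
- Cohort 3: 1 × 8 = 8 months
- Cohort 4: 0 months, so no transition can be observed

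Dementia at entry is an exclusion criterion (Table 1), so every event must arise in this time.

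**3. Illustrative events.** The documents give neither cohort sizes nor a dementia rate. The assumptions here are 60 per cohort (240/4), no dropout, everyone at risk, and 3, 5 or 10% per year.

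Person-years = 60 × (24 + 16 + 8 + 0)/12 = 240.

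**4. Detectable hazard ratio.** One continuous predictor, two-sided α = .05 without correction, 80% power: log HR per SD = (1.96 + 0.84)/√events.

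| Rate per year | Events | log HR | HR per SD |
|---|---|---|---|
| 3% | 240 × .03 ≈ 7 | 2.80/√7 = 1.06 | 2.9 |
| 5% | 240 × .05 = 12 | 2.80/√12 = 0.81 | 2.2 |
| 10% | 240 × .10 = 24 | 2.80/√24 = 0.57 | 1.8 |

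For comparison, HR 1.5 per SD needs (2.80/ln 1.5)² ≈ 48 events. HR 2 for a marker that splits the sample 50:50 needs 66.

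**5. Sensitivity to the assumptions.**
- If 20% of person-time is lost: 240 × .8 = 192 person-years, about 6 to 19 events.
- If only SCI, pMCI and MCI participants count, at an assumed 33% or 67% of the sample: about 79 or 161 person-years. That gives about 2 to 8 or 5 to 16 events at the same rates.
- If all 240 were followed for 24 months, which Table 2 does not allow: 480 person-years and about 14 to 48 events. The detectable HR per SD is then 2.80/√14.4 = 0.74, or 2.1, down to 2.80/√48 = 0.40, or 1.5.

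**6. The decline definition set against the question.** The listed changes are CHI to SCI, pMCI or MCI; SCI to pMCI or MCI; and pMCI or MCI to dementia. A participant who is SCI at one visit and has dementia at the next matches none of them. The same holds for CHI to dementia.

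**The case against.** The sample size section names its outcome openly. A reader might infer that the protocol claims 80% power for the dementia question; it does not. Nor is the powered outcome foreign to the aims. The objective sentence pairs cognitive decline with dementia, regression on decline is the first analysis listed, and decline contains pMCI or MCI to dementia. The conclusion section also concedes that decline cannot be observed over an extended period. All of this stands, and it makes this a matter of alignment rather than a false claim. It does not turn the .80 into power for a Cox analysis of dementia.

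It is also tempting to say that the Cox model will be overfitted, with some six confounders and markers from four domains. The documents do not support that. The confounders are named as examples in a general sentence not tied to the Cox model, and nothing says that the four domains enter one joint model. Overfitting is a risk, not a certainty.

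A flat statement that dementia will be rare also goes too far. Participants are 80 or older, some have MCI at entry, and the study can classify dementia itself from MoCA and CERAD-Plus. The event counts rest on assumed rates and cohort sizes.

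On the definition, an analyst might count a move from SCI to dementia anyway. Someone who meets the study's own dementia rule also satisfies the MCI row of Table 3. That route is not written down, and it need not hold for a diagnosis made outside the study.

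**Conclusion.** The point holds in a limited form. The single power statement covers cognitive decline; it serves the wider objective but not the main research question as worded. That conclusion rests on the text alone.

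The size of the shortfall for dementia is illustrative. With equal cohorts, no dropout, everyone at risk and 3 to 10% per year, about 7 to 24 events would be expected, and only hazard ratios of about 2.9 to 1.8 per SD would be detectable with 80% power. Restricting to SCI, pMCI and MCI or allowing for dropout lowers the event count; larger early cohorts or a higher rate would raise it.

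The gap in the definition needs no assumption: as written, SCI to dementia, which is part of the main question, and CHI to dementia do not count as decline.

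**What to change.** 1. Under Sample size, state that the .80 applies to cognitive decline and not to transition to dementia.
2. Under Study aims, align the confirmatory question with cognitive decline. Label the dementia Cox analysis exploratory, report it with confidence intervals, and keep the number of model terms in line with the events observed.
3. Under Cognitive status, add SCI to dementia and CHI to dementia to the changes that count as decline.

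If the sponsor prefers to keep dementia as the confirmatory question, the alternative to the first two steps is an event-based power statement that uses the actual follow-up of each cohort.

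The three changes are wording only. They make the claim about dementia more modest and need no extra participants.

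### Including 240 participants at the expected 20% dropout leaves 192 for analysis, 8 short of the 200 the article says are needed; a minor correction to the stated figures

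*Protocol article*

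**What the plan says.** The Sample size section of the protocol article gives the whole calculation in a few lines. It names the outcome: "The sample size calculation was based on the outcome cognitive decline". It describes the effect in words only: "small to moderate effect sizes are expected". It reports that a G*Power analysis "showed that 200 participants are required for analysis with α = .05 and power = .80". It then makes the allowance for loss: "Expecting a 20% dropout rate during the study period, 240 participants will be included".

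Three numbers therefore stand side by side: 200 to be analysed, 20% expected to be lost, 240 to be included. No other section gives a different target, a different dropout rate, a different base for the rate, or a further allowance.

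**The concern.** A dropout allowance has one task: the number included, less the expected loss, should give the number that the power calculation needs. Participants can drop out only after they have been included, so the expected rate applies to those included. The required inclusion number is then the analysable number divided by one minus the rate. Multiplying the analysable number by one plus the rate is a common slip and always falls short.

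The stated power of .80 is attached to 200 analysed participants. If the study recruits exactly as planned and loses exactly the proportion it expects, it ends below that number, and .80 is no longer the power that the stated plan supports. The Sample size section is where a reader looks to learn how much loss the study can absorb, and as written it overstates that margin.

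**Working it through.** **Inputs, all from the Sample size section**

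- Number needed in the analysis: 200
- Expected dropout: 20%
- Number to be included: 240
- Alpha .05 (sidedness not stated), power .80
- Effect size: no numeric value; test family and number of predictors not stated

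**Step 1. Reproduce the stated figure.** 200 x (1 + 0.20) = 240. This matches exactly. The article shows no formula, so that this is how 240 was obtained is an inference, though a likely one.

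**Step 2. Apply the stated dropout to the stated inclusion number.** 240 x (1 - 0.20) = 192. Shortfall: 200 - 192 = 8, and 8 / 200 = 4%.

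**Step 3. Find the inclusion number that fits the other two figures.** 200 / (1 - 0.20) = 200 / 0.80 = 250. Check: 250 x 0.80 = 200. This is 10 more than 240. Rounding does not explain the gap, because both 240 and 250 are exact results of their formulas.

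**Step 4. Find the dropout that 240 does cover.** 1 - 200 / 240 = 0.167, or 16.7%.

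**Step 5. Size the effect on power.** The 200 cannot be reproduced from the article, because the effect size and test are not given. The loss can still be gauged by assuming that 200 gives power of exactly .80 and asking what 192 gives for the same effect.

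*Normal approximation, two-sided alpha .05.* The standardised effect at 200 is 1.960 + 0.842 = 2.802. At 192 it is 2.802 x sqrt(192 / 200) = 2.745. Power = Phi(2.745 - 1.960) = Phi(0.785) = .784. A one-sided test gives .786.

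*Multiple-regression F test of all predictors together.* Effect size f2 is set so that N = 200 gives .80, with noncentrality f2 x N and N - p - 1 denominator degrees of freedom:

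| Assumed predictors p | f2 giving .80 at N = 200 | Power at N = 192 |
|---|---|---|
| 1 | 0.0396 | .7836 |
| 3 | 0.0556 | .7815 |
| 5 | 0.0660 | .7804 |
| 10 | 0.0852 | .7786 |
| 15 | 0.1005 | .7774 |
| 20 | 0.1140 | .7763 |
| 30 | 0.1386 | .7745 |

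The loss is roughly 1.5 to 2.5 percentage points of power across this range. Steps 1 to 4 do not depend on any of the assumptions in step 5.

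**The case against.** Four points can be made for the plan.

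*The 20% might mean 20% of the 200, that is, 40 people.* Then 240 would be right. The article does not say so, and a dropout rate over the study period is ordinarily a proportion of those who entered. Forty lost out of 240 is 16.7%. If that was meant, the sentence still needs rewording.

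*Not every dropout is lost to analysis.* The Statistical analyses section also plans mixed-effects models and a Cox model, both of which can use participants with incomplete follow-up. It leaves the handling of missing data until its amount and pattern are known. Someone in Cohort 1 or 2 who leaves after T2 can still contribute change data. This stands, and it means that more than 192 may contribute to some models. It does not repair the Sample size section, which relies on including more people, not on partial data, to reach 200.

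*The benchmark is soft.* With the effect described only as small to moderate, uncertainty about the effect size would move power far more than 8 participants do. This also stands, and it limits how much weight the shortfall can carry. A condensed article may leave those inputs to the full protocol, so their absence is not held against it here.

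*The consequence is small.* This is correct. No outcome, group definition or model changes, and the remedy is a matter of wording.

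**Conclusion.** The inconsistency is real. On the ordinary reading of a dropout rate, 240 included and 20% lost leaves 192, not 200; 240 covers 16.7%, and 250 is the number that fits. This rests only on figures in the Sample size section.

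The size is modest: 8 participants, and power of about .775 to .784 in place of .80. The power range assumes that 200 gives exactly .80 and that the test is a regression F test with 1 to 30 predictors, neither of which the article states. This is a minor arithmetic correction.

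Two stronger readings are tempting and are not supported. A reader might infer that the study is seriously underpowered because of this slip; a loss of about 2 points does not show that. A reader might also add that Cohort 4, which Table 2 shows as measured only at T1, deepens the shortfall, since decline is defined as a change of status. The article gives no cohort sizes, so no such loss can be quantified. That is a separate matter, which this point neither needs nor establishes.

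**What to change.** Reword the sentence on dropout so that the three numbers agree. Either of these is enough:

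- keep 240, state that 192 are expected to be analysable at 20% dropout, and give the power for 192 from the original G*Power settings (slightly below .80; about .775 to .784 under the assumptions above); or
- keep 240 and 200, and state that 240 allows for 16.7% dropout.

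For reference, 250 is the inclusion number consistent with 200 analysable at 20% dropout. Enrolling more participants is not needed to correct the statement.

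The cost is one sentence, one rerun of the power program if the first option is taken, and a slightly less favourable stated power or dropout margin. Recruitment, the visit schedule and the analysis are unaffected.
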